### Safety outcome measures

The incidence of adverse events (AEs) during the trial is the primary safety outcome measure. In addition, vital signs and laboratory tests before and after medication are monitored. Vital signs refer to temperature, heart rate, respiration, and blood pressure. Laboratory tests include blood, urine, hepatic and renal functions, electrocardiography, and C-reactive protein (inspect only at pre-medication). If the child is unable to cooperate or strongly disagree with the test for non-clinical need, such as hepatic and renal functions, the researcher must respect the patient’s wishes and record the reason for missing safety data on subject medical record with parents’ signature. All abnormal safety measure should be followed up until recover or return to pre-medication levels.

#### Record, assessment, management, and report of AE

The researcher should truthfully record all AEs related to children in subject medical record and CRF, including occurrence time, end time, duration, severity, therapeutic measures, outcome, and relationship with experimental drug.

The severity of AE can be graded according to the National Cancer Institute Common Terminology Criteria for Adverse Events (NGI-GTCAE) V.5.0 [21]. If it does not apply to certain specific AEs, the researchers will use the 5-level criteria from mild to death. Relationships between AE and experimental drug can be divided into definitely related, probably related, possibly related, probably not related, need further evaluated, and unknown. The first 4 cases will be considered as adverse drug reactions according to *adverse drug reactions report and monitoring manual* [22].

When AEs occur, researchers should make timely response measures, if necessary, can break blind procedure, and report to the sponsor and the clinical research associate. The sponsor is responsible for monitoring and reporting safety information and shall promptly report serious adverse events to all researchers, clinical trial institutions, ethics committees, and adverse reaction monitoring agency. Report of AEs shall be in accordance with the *Rapid reporting standards and procedures for safety data during drug clinical trials* issued by China’s center for drug evaluation, National Medical Products Administration (NMPA) [23].

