### Randomization, concealment, and masking

Randomization (1:1) will be stratified by study site, and the randomization list is generated by an independent statistician using SAS v 9.2. Two hundred forty children are divided into 40 blocks with the block size as 6. The documents of random process and randomization list will be enclosed in an opaque envelop. Participants, researchers, and coordinators together with statisticians were not aware of the allocation of the patient and remained unaware until trial completion. All study sites will also receive opaque envelopes containing the experimental drug’s website, login ID, password, instructions, security information, and treatment recommendations, which the researchers should open in an emergency.

In this trial, we use a very low dose (5%) of KHJS solution as a placebo spray. It contains 0.525 g/15 ml of crude herbs, while KHJS contains 10.05 g/15 ml crude herbs. Both the KHJSs and placebo sprays are manufactured by Guizhou Sanli Pharmaceutical Co., Ltd. with the same specification, appearance and flavor. These sprays are coded, packed, and labeled based on randomization list. Each center has an independent drug administrator responsible for the storage, distribution, recovery, and documentation of all experimental drugs.

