### Sample size calculation

Based on the primary outcome, the software PASS15.0 is used to calculate the sample size. According to relevant literature and previous studies [24], the median time of producing analgesic effect in the experimental group is 10 min, and that in the control group is 20 min. Set α as 0.025, β as 0.2, and the optimal bound value as 0. Taking into account the 10% loss to follow-up rate, the final estimated sample size is 105 cases per group. After comprehensive consideration, the final decision of each group of 120 cases, a total of 240 cases.

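### The causality rule counts events judged 'probably not related' as adverse drug reactions and offers no 'unrelated' category, so a reaction rate built on it would not separate reactions from adverse events

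*Protocol article*

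**What the plan says.** The rule stands in the protocol article under 'Record, assessment, management, and report of AE'. The relationship of an AE to the study drug takes one of six values, in this order: "definitely related, probably related, possibly related, probably not related, need further evaluated, and unknown". The end of that list runs directly into the rule: "possibly related, probably not related, need further evaluated, and unknown. The first 4 cases will be considered as adverse drug reactions". The rule is attributed to a cited reaction-monitoring manual. The same section requires complete capture, with relationship to the drug among the recorded items: "The researcher should truthfully record all AEs related to children in subject medical record and CRF".

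Under 'Safety outcome measures' the main safety endpoint does not depend on causality: "The incidence of adverse events (AEs) during the trial is the primary safety outcome measure". The other safety measures named there are vital signs and laboratory tests. The article lists no adverse drug reaction rate among its outcomes.

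On the control arm, 'Randomization, concealment, and masking' says: "we use a very low dose (5%) of KHJS solution as a placebo spray". Both arms therefore receive some active product, and attribution matters in both.

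**The concern.** A causality scale is there to separate events plausibly due to the drug from those that are not. Here the fourth level states that the drug is probably not the cause, and the next sentence makes that level a drug reaction. With no 'unrelated' level, an investigator who is confident that an event belongs to the illness has no accurate box. The nearest one, 'probably not related', counts as a reaction. The only levels outside the reaction class are the two in which no judgement has been reached.

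Such events are foreseeable in this trial. 'Patient population and setting' describes fever, headache and poor appetite as features of the disease, and treatment is planned for up to five days. The Background supports the product's safety with an adverse reaction incidence below 0.01% for 2017 to 2019. A reaction rate from this trial would invite comparison with that figure, but the comparison would be hard to interpret if the trial's rate contains events judged probably not due to the drug. 'Ethical requirement' also ties the sponsor's payment for treatment to reactions caused by the drug, so the definition may matter outside the analysis too.

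**Working it through.** **Step 1: apply the rule to the list.**

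| Order | Level | Counts as a reaction under the rule? |
|---|---|---|
| 1 | definitely related | yes |
| 2 | probably related | yes |
| 3 | possibly related | yes |
| 4 | probably not related | yes |
| 5 | need further evaluated | no |
| 6 | unknown | no |

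All four levels that express a judgement count. The two that express none do not. Nothing elsewhere in the article changes this.

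**Step 2: is there a stated figure to reproduce?** No. The article gives no AE rate, reaction rate, sample size or power that uses the rule. What follows is illustration only.

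**Step 3: formulas.** Let *a* be the AE rate (one AE per child assumed), *p* the share of AEs judged 'probably not related', and *u* the share left at 'need further evaluated' or 'unknown'.

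- Rule as written: *a*(1 − *u*)
- First three levels only: *a*(1 − *p* − *u*)
- First three levels plus unassessed events: *a*(1 − *p*)

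The rule therefore exceeds the first-three count by *a·p*. Against the first three plus unassessed, it differs by *a*(*p* − *u*), which can take either sign. If *u* = 0, the rule gives *a* itself: the reaction rate equals the AE rate.

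**Step 4: numbers.** The group size of 120 is from 'Sample size calculation' ("the final decision of each group of 120 cases, a total of 240 cases"). The AE count and the shares are assumptions. With 12 AEs, *a* = 12/120 = 10%.

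| *p* | *u* | Rule as written | First three | First three + unassessed |
|---|---|---|---|---|
| 10% | 0 | 10.0% | 9.0% | 9.0% |
| 30% | 0 | 10.0% | 7.0% | 7.0% |
| 50% | 0 | 10.0% | 5.0% | 5.0% |
| 70% | 0 | 10.0% | 3.0% | 3.0% |
| 30% | 10% | 9.0% | 6.0% | 7.0% |
| 10% | 10% | 9.0% | 8.0% | 9.0% |
| 10% | 20% | 8.0% | 7.0% | 9.0% |

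With *u* = 0 the excess over the first three levels is 0.10 × 0.10 = 1 point up to 0.10 × 0.70 = 7 points. At an AE rate of 5% (6/120) the same shares give 0.5 to 3.5 points, and at 20% (24/120) they give 2 to 14 points.

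The last three rows show the direction problem. Against a count that keeps unassessed events, the rule is 2 points too high, equal, and 1 point too low respectively.

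**The case against.** The strongest reply is that nothing declared in the trial uses this rule. The primary safety outcome is the incidence of all AEs, no reaction rate is named as an outcome, and prompt reporting by the sponsor is tied to serious adverse events rather than to reaction status. That is correct, and it limits the severity.

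The rule is also attributed to a manual that is not to hand. Whether the article miscounted, mistranslated or followed its source cannot be checked. This stands too, but it does not remove the contradiction between label and rule in the text itself. Nor is this detail left to a fuller document: the rule is stated, and it misclassifies.

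Three stronger readings are tempting, and the documents do not support them:

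- A reader might infer that events of unknown cause are lost. They are not. All AEs are to be recorded, so unassessed events stay in the data and in the primary safety outcome. They are outside the reaction class only, and 'need further evaluated' is treated in the same way as 'unknown'.
- A reader might infer a large fixed inflation, for instance 1/(1 − 0.7) = 3.3-fold if 70% of events are 'probably not related'. That share is an assumption, and the multiple also requires that no event is unassessed.
- A reader might infer that a true difference between arms would be hidden. Adding the same background to both arms pulls their ratio towards 1 but leaves their difference unchanged. With assumed reactions of 6% v 2% and 15% background in each arm, the ratio falls from 3.0 to 21/17 = 1.24, while the difference stays at 4 points. The same dilution is present in the all-AE comparison that the protocol chose as primary.

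**Conclusion.** The point holds as an internal contradiction in a stated rule. Read literally, it makes a reaction of every AE that receives a causality judgement, including those judged probably not due to the drug, and leaves out those without a judgement. A reaction rate derived from it would be unreliable as a measure of drug reactions, and with no unassessed events it would simply equal the AE rate.

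The size cannot be fixed from the article. Against the first three levels, the excess is the AE rate times the share judged 'probably not related': 1 to 7 points at an assumed 10% AE rate, one AE per child, no unassessed events and shares of 10% to 70%. Against a count that also includes unassessed events, even the direction depends on the shares.

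It does not follow that the trial's safety result will be wrong. All-AE incidence is unaffected, and the article does not commit to reporting a reaction rate. Severity is minor to moderate.

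**What to change.** Reconcile the six-level list, the reaction rule and the cited manual so that 'probably not related' no longer counts. Adverse drug reactions would then be the definitely, probably and possibly related events. State before unblinding how 'need further evaluated' and 'unknown' events are handled, for example with a sensitivity count that adds them to the reactions. If the CRF is still open, add a 'not related' option.

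The cost is small. Relationship is already recorded for each AE, so the reaction count can be redefined at analysis without new data. The blinded data verification meeting before database lock, described under 'Data collection, management, monitoring, and auditing', is the latest natural point to do so. The CRF change is less certain. Recruitment was scheduled for June to December 2020 and the article appeared in March 2021, so if recruitment ran to schedule, a new option would mean reassessing events already recorded. In that case the change of definition alone is enough. An ethics notification may be needed, since 'Ethical requirement' asks for resubmission of significant modifications.

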### Schedule of study procedures

Figure 2 is the schedule of screening, enrollment, intervention, assessments, and data collection.

**Fig. 2 Fig2:**
[figure not shown]
Schedule of study procedures. √○, children will be evaluated for WBS score (5, 10, 20, 30, 40, 50, 60, 90, 120, 150, and 180 min after the first dose) by researchers in the hospital; √△, children will be evaluated for WBS score (full 1, 2, 3, 4, 5 days) by the child’s parents/caregiver at home; √*, if there is an AE, the patient needs to be followed up for safety information till reach the endpoint of event

### Sample size calculation

Based on the primary outcome, the software PASS15.0 is used to calculate the sample size. According to relevant literature and previous studies [24], the median time of producing analgesic effect in the experimental group is 10 min, and that in the control group is 20 min. Set α as 0.025, β as 0.2, and the optimal bound value as 0. Taking into account the 10% loss to follow-up rate, the final estimated sample size is 105 cases per group. After comprehensive consideration, the final decision of each group of 120 cases, a total of 240 cases.

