### Statistical analysis

In this experiment, the superiority trial design is adopted. Full analysis set (FAS) included all children who were randomized, received at least one spray of medication, and had at least one visit record. Per-protocol set (PPS) includes only patients who fulfill the protocol. All subjects who have taken the experimental drug will have their data covered by the safety set (SS) if the safety results are recorded. FAS and PPS are selected for effectiveness evaluation, and SS is selected for safety evaluation. If there are missing values in the primary outcome, the method of carrying forward the last observation data to the final results of the trial is adopted. An independent statistician will use SAS v 9.2 for statistical analysis. All hypothesis tests are conducted by two-sided test, and the overall comparison inspection level is 0.05 of α.

Survival data will be statistically described by median, upper quartile, lower quartile survival time, and 95% confidence interval (95% CI), and survival curve will be made. The comparison between groups is checked by log-rank test. If the influence of baseline factors is considered, Cox regression analysis is adopted. For quantitative data, the number of cases, mean, standard deviation, minimum, median, maximum, upper quartile, lower quartile, and 95% CI are used to describe the data. *T* test or paired *t* test is used for statistical analysis of data before and after treatment in two groups or within groups. If the influence of center or other confounding factors are considered, analysis of covariance is used.

For qualitative data, frequency table, percentage, or composition ratio is used to describe the data. For statistical analysis of data before and after treatment in two groups or within groups, *χ*^2^ test, Fisher’s exact probability method, Wilcoxon rank sum test, or Wilcoxon’s sign rank sum test is used. For the comparison of two categories and ranked data, if the influence of center or other factors are considered, CMHχ^2^ test is adopted. If the influence of confounding factors is considered, logistic regression analysis is adopted.

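### The 105 children per group cannot be reproduced from the printed inputs; under the usual exponential assumption they give about 37–40 per group

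*Protocol article*

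**What the plan says.** The protocol article's section on sample size calculation rests the size on the primary outcome, time to analgesic onset. Its effect assumption is that "the median time of producing analgesic effect in the experimental group is 10 min, and that in the control group is 20 min". The remaining settings are "Set α as 0.025, β as 0.2, and the optimal bound value as 0". The result is "Taking into account the 10% loss to follow-up rate, the final estimated sample size is 105 cases per group", which is then raised on general grounds to 120 per group, 240 in all. PASS 15.0 is named. No hazard ratio, distribution, onset rate or sidedness is given.

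Other sections supply the rest of the design:

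- Primary outcome: pain is scored at baseline and at 11 times after the first dose, the last at 180 min.
- Statistical analysis, on survival data: "The comparison between groups is checked by log-rank test".
- Statistical analysis, on the test level: "All hypothesis tests are conducted by two-sided test, and the overall comparison inspection level is 0.05 of α".
- Statistical analysis, on the aim: "In this experiment, the superiority trial design is adopted".
- Randomization: "Randomization (1:1) will be stratified by study site".

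**The concern.** A halving of the median time to onset is a large effect, and nearly every child would be expected to reach onset within a 3-hour window if the medians are 10 and 20 min. A log-rank comparison with those features needs few children, so 105 per group looks far too many for 80% power.

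What is at stake is the meaning of the design. If 10 v 20 min is the real assumption, the declared 80% power is not the power of this trial. If a smaller effect lies behind 105, readers and ethics committees have been given the wrong design effect. Either way they cannot tell which difference the trial was sized to detect.

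**Working it through.** **Inputs from the article.** Medians 10 and 20 min; alpha 0.025; beta 0.2; bound 0; 10% loss; 1:1 allocation; log-rank test; observation to 180 min.

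**Assumptions added here.**
- Onset times are exponential, so the hazard ratio (HR) is 20/10 = 2.
- Alpha 0.025 is one-sided. Its critical value, 1.96, is also that of the two-sided 0.05 in the analysis section.

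**Step 1: events needed.** (1.960 + 0.842)² = 7.849.
- Schoenfeld: 4 × 7.849 / (ln 2)² = 65.3, so 66 events.
- Freedman: [(2 + 1)/(2 − 1)]² × 7.849 = 70.6, so 71 events.

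**Step 2: proportion with onset by 180 min.** 1 − ½(2^(−180/10) + 2^(−180/20)) = 1 − ½(0.000004 + 0.00195) = 0.999.

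**Step 3: children per group.**
- Schoenfeld: 65.3 / 2 / 0.999 = 32.7; divided by 0.9 = 36.3.
- Freedman: 70.6 / 2 / 0.999 = 35.4; divided by 0.9 = 39.3.

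Allowing for rounding, this is 37–40 per group. The stated 105 is about 2.6 to 2.8 times as large. As a check, a simulated log-rank test on the article's own assessment times gave 80.5% power at 36 evaluable children per group.

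**Step 4: attempts to reach 105.**

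| Variant | Per group, with 10% loss |
|---|---|
| Alpha 0.025 read as two-sided, 180 min | 44–49 |
| Hazard-difference formulas, 180 min | 42–45 |
| HR 2, only the onsets by 20 min counted (62.5% of children) | 59–64 |
| As above, two-sided 0.025 | 72–77 |
| Two proportions at 10 min (50% v 29.3%), continuity-corrected | 107 |

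The last row is close, but it is neither the stated outcome nor the stated test. At HR 2 with critical value 1.96, a result of 105 needs only about 35–37% of children to reach onset (65.3/189 to 70.6/189). That means a cut-off of about 8.4 min (Schoenfeld) to 9.3 min (Freedman), below either median and against the 180 min in the article.

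**Step 5: what 105 and 120 deliver.** Nearly all retained children are taken to have an onset.
- 105 × 0.9 × 2 = 189 events. Power at HR 2 = Φ(√189 × ln 2 / 2 − 1.96) = 99.7%. The HR with 80% power is exp(2 × 2.802/√189) = 1.50, for example medians of about 13.3 v 20 min.
- 120 × 0.9 × 2 = 216 events. Power at HR 2 = 99.9%. The HR with 80% power is exp(2 × 2.802/√216) = 1.46.

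**Step 6: does the distribution matter?** Take a Weibull model with common shape 0.6 and the same two medians.
- HR = 2^0.6 = 1.52.
- Onset by 180 min: 1 − ½(e^(−0.693 × 9^0.6) + e^(−0.693 × 18^0.6)) = about 95%.
- Schoenfeld: 4 × 7.849 / (0.6 × ln 2)² = 181.5 events; 181.5 / 2 / 0.953 / 0.9 = 106 per group.
- Freedman: 109 per group.

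An unprinted distributional input can therefore bring the stated medians close to 105.

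**The case against.** The strongest reply is that two medians fix the hazard ratio only under an exponential model, and the article names no distribution. Step 6 shows that a plausible alternative gives 106–109 with the same medians, power, loss and 180 min. This stands. It rules out the inference that 105 is necessarily a miscalculation, or that the true assumption must have been medians nearer 13.3 v 20 min. It does not make the figure reproducible: the exponential model is the usual one when medians are entered, and the article prints nothing that would lead a reader to another.

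The sidedness of alpha 0.025 is also an inference. The other reading moves the result only to 44–49.

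A condensed article may leave the software procedure and its settings to the full protocol, so their absence is not the defect. The defect is that the printed inputs and the printed result do not agree.

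A reader might also infer that the trial exposes about three times the children it needs. The documents do not support this. The comparison concerns the primary efficacy test alone; the trial also has a stated safety objective, and the final 240 was set deliberately above the calculated figure.

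**Conclusion.** The point holds as one of reproducibility and reporting, of moderate weight. Assuming exponential times and a critical value of 1.96, the printed inputs lead to about 37–40 per group, not 105, and the planned size has over 99% power at the stated medians rather than 80%. The effect assumption, the calculation or an unreported input accounts for the gap; the article does not allow a choice among the three.

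It would be wrong to conclude that the trial is underpowered or its result compromised. At 10 v 20 min the error, if it is one, runs towards more power, and neither the primary test nor its type I error is affected.

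**What to change.** Rewrite the sample size paragraph so that its inputs yield its result. There are two ways:

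- keep 105 and give the hazard ratio or distribution that produces it (for example HR about 1.5); or
- keep 10 v 20 min as the basis and correct the calculated figure (about 37–40 per group if exponential times were meant).

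In either case, say whether alpha 0.025 is one-sided, and state the power of 240 children at the chosen effect. With exponential times and 10% loss, that is about 99.9% at HR 2, or 80% at HR 1.46.

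The cost is one paragraph. Enrolment and analysis stay as they are.

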### Data collection, management, monitoring, and auditing

Before the start of the trial, each study site should hold the project kick-off meeting respectively to strengthen the researchers and quality control personnel to master the trial plan and the operation technology of the key nodes. In addition, researchers should be trained specifically in the methodology of indicator evaluation.

In this study, we designed subject medical record and subject diary to record the first-hand clinical trial data of children. Researchers or clinical research coordinator (CRC) should collect relevant information and record it on the subject medical record timely, completely, and accurately. The subject diary is used to record the WBS score and the experimental drug use of the children. In order to improve compliance of the children until completion of the trial, we will strengthen patient management by assigning investigators one-on-one follow-up.

The data manager will design electronic CRF according to the trial plan and provide an input guidance. The trained CRC shall enter information from the subject medical record and subject diary into the electronic CRF within 3 days of each visit. This trial is designed to encode AEs and concomitant medication on electronic CRF. Medical coders coded the AEs according to MedDRA 22.0, and the concomitant medication code was classified by WHO ATC (World Health Organization, Anatomical Therapeutic Chemical classification). The database setup follows CDISC standard, linked with electronic CRF and relying on electronic data capture system which has logic verification and data capture function. Data manager will clean and verify the database according to the data verification plan previously written after finishing data collection and suspicious data to researchers circularly till all questions are answered. After that, researchers, data managers, and statisticians will hold a data verification meeting under the blind state for discussing data process and the partition of data sets. Once the agreement is reached, the database is locked and no modifications are allowed thereafter. After the completion of the trial, the documents involved in the whole trial shall be kept until at least 2 years after the termination of the clinical trial.

Since KHJS has more than 10 years of good clinical experience, and considering the funding and time constraints of the project, there will be no interim analysis. To ensure the quality of the clinical trial, an independent expert committee consisting of clinical experts, statisticians, pharmaceutical experts, pharmacology, and toxicology experts will be established to monitor and evaluate patient safety and efficacy data in a blind manner. It will also assess whether participants received good clinical care and safety issues explained and properly resolved, as well as recommendations for protocol modifications or even recommendations and decisions to terminate the study based on efficacy and safety.

Auditors independent of the researchers and sponsors will conduct monthly reviews to systematically review the activities and documents related to the study to evaluate whether the study was conducted in accordance with the study protocol, GCP, and relevant regulatory requirements and whether the trial data is recorded in a timely, true, accurate, and complete manner.

